### Trial design and randomisation (Figure 1)

**Figure 1 F1:**
[figure not shown]
**Trial design**.

This is a prospective, randomised, controlled clinical trial conducted at two neighbouring Trusts in the Anglia Cancer Network: Addenbrooke's Hospital (CUH) and West Suffolk Hospital (WSH). Patients meeting the defined eligibility criteria are invited to take part in the study prior to or during their planned cancer treatment. All patients taking part provide written informed consent. Patients are randomised on a 1:1:1 basis to one of 3 arms: treatment delivered in the hospital out-patient and day unit environment (control arm A), treatment delivered at home (arm B) or treatment delivered in a GP surgery (arm C) using the method of minimisation with a random element to the assignment. Randomisation is performed centrally by statisticians located separately from trial recruitment and co-ordination and without knowledge of patients or their characteristics.

In the minimisation procedure the patients are stratified by centre (CUH or WSH), by treatment intent (cure, palliation in terms of disease control and life prolongation, or supportive care aimed at symptom control), ECOG performance status (PS 0, 1 or 2), gender, and prior cancer drug treatment (yes or no).

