### Study procedures

The study procedures are summarised in Table 1.

**Table 1 T1:** Study measures and timing

	Data point 1: Baseline, prior to commencing treatment	Data point 2: 4** weeks into treatment	Data point 3: 8** weeks into treatment	Data point 4: 12 weeks into treatment	Data point 5: 24*** weeks into treatment
Clinic Review*	x			x	X

PS	x	x	x	x	X

Weight	x	x	x	x	

Blood tests*	x				

Radiology*	x				

EORTC QLQC30.	x	x	x	x	X

HAD, EQ-5D and Patient Satisfaction Questionnaire	x	x	x	x	X

CSRI Completion	x			x	

Patient Diary for AE Recording	x	x	x	x	X

Semi-Structured Interview	x(1 in 10 patients)			x	

*Clinic review, blood tests and radiological investigations will be carried out according to standard clinical practice at baseline and during the study period.

** +/- 1 Week

*** For patients whose treatment continues beyond 12 weeks, patients will complete a further set of trial assessments when their treatment stops or at 24 weeks, whichever is sooner. This data point is optional.

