Unit costs are attached to the service use data to produce service costs for each patient in the study. The costs of delivering treatment in hospital, GP surgeries and at home are derived from information on salary costs, administrative and capital overheads, and drug costs. The unit costs of other services are obtained from nationally applicable data [16]. The cost of a home care worker is used to value care provided by family members/friends. Travel time costs are estimated using wage rates for those in employment and a proportion of this for those who are not in work.

Costs are compared between the three groups using bootstrap methods to account for the likely non-normal distribution of the data. Cost-effectiveness is assessed by combining service cost data with the primary outcome measure (QLQ-C30) and also Quality Adjusted Life Year (QALYs) generated from the EQ-5D [17]. Two-way comparisons are made between the groups. If one group has lower costs and better outcome over another then it would be dominant. If costs are higher and outcome better then incremental cost-effectiveness ratios would be constructed which will show the extra cost incurred to achieve an extra unit of outcome. To address uncertainty in the cost and outcome differences, cost-effectiveness acceptability curves are used which will show the probability that one option is more cost-effective than another for different values placed on a unit improvement in outcome.

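### Cost-effectiveness of three competing venues is assessed only in pairs, so the acceptability curves do not show how likely each venue is to be the best of the three

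*Protocol article*

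**What the plan says.** In the Protocol article, Trial design and randomisation, "Patients are randomised on a 1:1:1 basis to one of 3 arms": hospital, home or GP surgery. The third secondary aim concerns costs and cost-effectiveness across all three locations, and the Background gives better-informed commissioning as the reason for the study.

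The economic method is in section iii), Service use and cost data. Costs are handled across the arms: "Costs are compared between the three groups using bootstrap methods to account for the likely non-normal distribution of the data". Cost-effectiveness then combines costs with the QLQ-C30 and with QALYs from the EQ-5D, and is examined in pairs: "Two-way comparisons are made between the groups". Two reading rules follow: "If one group has lower costs and better outcome over another then it would be dominant", and "If costs are higher and outcome better then incremental cost-effectiveness ratios would be constructed". Uncertainty is shown by acceptability curves giving "the probability that one option is more cost-effective than another for different values placed on a unit improvement in outcome". The section names no joint ranking of the three arms, no check for extended dominance, and no probability that each venue is the most cost-effective of the three.

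**The concern.** A commissioner chooses one venue from three for a given patient group. The relevant uncertainty statement is the probability that a venue has the highest net benefit among all three at a given threshold. A curve for home against hospital says nothing about GP surgery, and the three pairwise curves do not add up to a division of probability among the venues. If home and GP surgery perform similarly, both could be reported with high probabilities against hospital although neither is more likely than not to be the best choice. The primary hypothesis groups these two settings together, so that pattern is plausible.

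The same applies to ratios. With three options, the informative ratio compares an option with the next less costly option that is still in contention. A ratio against hospital alone can make an expensive venue look acceptable when a cheaper alternative offers more net benefit.

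This is a method that the text states, not a detail it leaves out.

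**Working it through.** **Figures in the plan.** The economic section gives no costs, QALYs, variances or threshold, so there is no stated figure to reproduce. The sample-size section does reproduce (91 evaluable per arm, and 91/0.70 = 130), but it concerns the QLQ-C30 and does not bear on this point. The numbers below are illustrations.

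**1. Pairwise probability against probability of being best**

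Assumptions: at a fixed threshold, the three arm-level mean net benefits have independent normal errors with equal standard errors, scaled to 1. Equal allocation makes this a natural starting case, but the documents do not give it.

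If a venue leads a rival by d, then P(venue beats rival) = Φ(d/√2), so d = √2 × z(p). For p = 0.80, d = 1.414 × 0.842 = 1.19.

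For a venue that leads both rivals by d, P(best) = ∫ φ(x − d) Φ(x)² dx.

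| Situation | Pairwise probability | Probability of being best of three |
|---|---|---|
| All three equal | 0.50 for every pair | 0.33 each |
| One venue ahead of two equal rivals | 0.70 against each | 0.56 |
| One venue ahead of two equal rivals | 0.80 against each | 0.69 |
| Home and GP surgery equal | each 0.80 against hospital | 0.46, 0.46; hospital 0.09 |
| Home and GP surgery equal | each 0.90 against hospital | 0.48, 0.48; hospital 0.03 |
| Venues evenly ordered | best: 0.80 against hospital, 0.66 against the second | 0.59 |

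**2. How far this depends on the error assumption**

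Some limits need no assumption about errors. If a venue beats each of two rivals with probability 0.80, its probability of beating both is at most 0.80 and at least 0.80 + 0.80 − 1 = 0.60. If home and GP surgery are exchangeable and each beats hospital with probability 0.80, hospital is best with probability between 0 and 0.20. Each community venue is then best with probability between (1 − 0.20)/2 = 0.40 and 1/2 = 0.50. So 0.69 and 0.46 depend on the assumptions, but the pairwise figures alone never fix the three-way probability.

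**3. Ratios against a non-adjacent comparator**

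Assumed costs and QALYs: A 1000, 0.100; B 1100, 0.108; C 1400, 0.118.

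- B against A: 100/0.008 = 12,500 per QALY.
- C against A: 400/0.018 = 22,222 per QALY.
- C against B: 300/0.010 = 30,000 per QALY.

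At an assumed threshold of 25,000, net benefit (25,000 × QALY − cost) is 1500 for A, 1600 for B and 1550 for C. C passes the threshold against A, yet B is the best option. The adjacent comparison, C against B, shows this.

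**4. Do the two reading rules leave a result uncovered?**

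For a pair X and Y there are four sign combinations. X cheaper and better: X dominates. X dearer and worse: Y dominates. X dearer and better: ratio for X over Y. X cheaper and worse: Y is dearer and better, so there is a ratio for Y over X. All four are covered.

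**The case against.** The best counter-argument is that nothing stated is false. The curves are described as one option against another and are never presented as the probability of being best of three. Mean net benefit is also transitive: if all three pairs are run and read at one threshold, the best venue by point estimate can be recovered, and extended dominance can be seen from the three ratios. Nothing prevents a joint plot from the same bootstrap samples. This stands as far as point estimates go. It does not supply the missing probability, because section 2 of the working shows that pairwise probabilities do not determine it.

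Three stronger readings are tempting but unsupported.

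- *The rules omit the cheaper-but-worse result.* They do not. They are worded for one group over another, not for community minus hospital, so that result is a ratio for the other member of the pair.
- *Costs and QALYs are analysed without baseline adjustment.* The economic section names no covariates, but it excludes none, and a bootstrapped regression would fit its wording. The Statistical Analysis section adjusts continuous outcomes for the stratifiers and the baseline of the outcome. Whether that rule extends to costs and QALYs is a detail that an article may leave to the full plan.
- *The plan will misstate which venue is best.* That follows only if ratios are read against a non-adjacent comparator, which the plan neither prescribes nor rules out.

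**Conclusion.** The point holds in a limited form. The Protocol article fixes a pairwise method for a three-way choice, and its acceptability curves will not show the probability that a venue is the best of the three. Under equal, independent errors, pairwise 0.80 against both rivals corresponds to 0.69 of being best, and two equal community venues at 0.80 against hospital to 0.46 each. Without that assumption the ranges are 0.60 to 0.80 and 0.40 to 0.50. The documents contain no economic figures, so the actual gap in this trial cannot be calculated. The risk of a misleading ratio is conditional on the comparator used. This is a worthwhile improvement to a secondary aim. The primary endpoint, its analysis and the sample size are not affected.

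**What to change.** In section iii), Service use and cost data, replace the two-way comparisons with a fully incremental three-arm analysis. Order the venues by mean cost, remove dominated and extendedly dominated options, and report ratios between adjacent remaining options. From the same bootstrap samples, calculate each arm's net benefit across the range of thresholds. Present one acceptability plot with a curve for each arm, showing the proportion of samples in which that arm has the highest net benefit; at each threshold the three curves sum to one. Pairwise results can stay as supporting detail.

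The cost is a change of wording and a little more analysis code. No additional data, patients or visits are needed.

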###### iv) *Patient safety*

CUH and WSH have in place a comprehensive set of policies and procedures governing community-based care. Specifically for cancer, the Cancer Treatment in the Community (CTC) policy identifies low risk patients and low risk treatments usually offered to patients in the hospital out-patient and day unit facilities which are potentially suitable for delivery in the community (Table 1). In addition, the CTC policy describes a clinical governance framework for ensuring patient safety in the community, reflecting standard policies and procedures adhered to when delivering cancer treatment in hospital. To be considered for this trial, both the patients and the treatment being offered are required to meet the criteria listed in the CTC Policy.

The treatments given to patients taking part in this trial are by definition those which are well established, with an excellent safety record. Our hypothesis is that patients would not be adversely affected or harmed by receiving treatment in the community. Appropriate safety measures and procedures are in place for community treatment, to provide a safe environment considered to be equivalent to the hospital setting.

Patient safety will be evaluated by recording the number of adverse and serious adverse events which occur during the study period (see safety procedures).

###### v) *Compliance with treatment delivered in the different locations*

Patient compliance with their treatment is monitored as per standard local practice.

###### vi) *Non-participation in study*

The reasons why patients might decide not to take part in this study are of considerable interest. A short, anonymised questionnaire is offered to any patient who declines to take part. The patients are under no obligation to complete the questionnaire. Exploration of the responses on the returned forms offers insight into patient concerns regarding such delivery options, and therefore an indicator as to the likely take-up of future community chemotherapy delivery programmes.

In addition, all patients are monitored for symptom control, tumour response and overall survival according to standard clinical practice.

###### vii) Impact of treatment on local GP resources

Once a patient has completed the trial, a letter is sent to the patient's own GP requesting review of the patient notes held at the local GP surgery to document: the number of occasions the patient contacted his or her GP surgery during the trial period; what type of surgery staff were involved on each occasion (e.g. GP, nurse, other); the nature of those contacts, by classifying them as being related to a) cancer treatment, b) other need for treatment of any kind, c) support services, d) advice, or e) other. In addition, a summary print-out of all prescriptions is requested. The GPs receive a small remuneration for providing this information.

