### Study interventions

The Investigator has primary responsibility for the welfare of the patient for the duration of the study, whether receiving treatment in hospital, at home or in the GP surgery. Patient treatment is governed by a single set of standard operating procedures in use at CUH, WSH (and the GP surgeries involved in this study.

The Investigator is responsible for prescribing all treatment for trial patients, but can delegate this task to a member of his or her junior staff, as is standard clinical practice.

The treatment study period for this trial is 12 weeks, since most treatments are expected to be prescribed for at least this period of time. All planned treatment for a study patient will be delivered in the location to which the patient is randomised. Treatment of patients within the community may be aborted and transferred to hospital in the event of significant problematic drug-related toxicities, occurrence of a serious adverse event (SAE), on request by the patient, or following discussion between the community chemotherapy nurse and the Investigator who may feel it is in the patient's best interest to do so. The Investigator will review the patient in clinic prior to study entry and on completion of the study (whether at 12 weeks, or sooner in the case of early withdrawal). For patients continuing treatment beyond 12 weeks, the Investigator will review the patient on completion of the planned treatment or at 24 weeks, whichever is sooner.

All anticancer treatment and other prescribed drugs are dispensed by the oncology pharmacists in the respective hospitals, according to local policies. On the designated day, prescribed drugs for patients receiving treatment in the community are dispensed and placed with a copy of the patient prescription sheet in a designated box, ready for collection by the community chemotherapy nurse from the oncology pharmacy at a previously arranged time. The prescription sheet copy is returned to the oncology pharmacy within 48 hours of treatment.

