### Concomitant medication

Patients may receive all concomitant therapy deemed to provide adequate supportive care. Since this trial is not directly interested in treatment *per se*, concomitant medications will not be systematically recorded. However, information about ongoing treatment at the time of study entry and changes in treatment during the course of the study will be recorded by the patient in the Client Service Receipt Inventory (CSRI). In addition, records of drugs prescribed by the hospital and the patient's own GP will be obtained.

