###### iii) *Service use and cost data*

Service use and cost data relating to patients, the NHS and society as a whole, is collected and compared for all arms of the study. Use of the specific cancer drug treatments is centrally recorded. Other service use data was collected using an adapted version of the CSRI [15]. The CSRI has been used in around 200 health economic studies of health and social care interventions in the UK and internationally. Service use information is typically provided by the patient and/or family members (supplemented where possible with administrative data from providers) and the objective is to allow comprehensive costs to be generated.

By means of the adapted CSRI, patients are asked to provide information on a range of services used, taking place at Baseline and at 12 weeks. Services include contacts with staff directly related to the delivery of cancer care (oncologists, nursing staff, hospital-based pharmacists, etc), plus other healthcare professionals (GPs, primary care nurses, psychologists, etc), and social care professionals. Time spent in hospital (overnight stays plus day-patient attendances) is recorded. In addition, time per week spent by family/friends providing care (broken down into specific tasks) to the patient because of their condition is recorded.

A key cost is thought to be related to time spent travelling by patients and/or staff, to receive or deliver treatment. Patients are asked to state where contacts take place and time spent travelling to use them and also mode of travel. Many patients are accompanied and the CSRI also records information on this. A further section in the CSRI records time taken off work by patients and family members specifically because of the condition and treatment.

Data is also collected from the chemotherapy nurses. They are asked to document all scheduled and unscheduled contact with their patients as well as working hours relating to treatment of trial patients.

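### The GP-notes request waits for trial completion and the only follow-up CSRI is at week 12, so GP-contact and patient-reported cost data can be lost or cut short for patients who die or withdraw, possibly unequally by arm

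*Protocol article*

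**What the plan says.** All references are to the protocol article.

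- **Impact of treatment on local GP resources:** the trigger for the notes request reads "Once a patient has completed the trial, a letter is sent to the patient's own GP requesting review of the patient notes". The GP is asked for the number of surgery contacts during the trial period, the staff involved, the reasons, and a print-out of prescriptions.
- **Service use and cost data:** for the CSRI, "patients are asked to provide information on a range of services used, taking place at Baseline and at 12 weeks". Table 1 (Study procedures) agrees: the row "CSRI Completion" is marked at data points 1 and 4 only.
- **Study interventions:** the investigator reviews each patient at entry and "on completion of the study (whether at 12 weeks, or sooner in the case of early withdrawal". No CSRI is attached to an early review.
- **Recording and collection of data:** a move from community to hospital treatment counts as an SAE and as withdrawal. Hospital-arm patients cannot move the other way.
- **Study duration:** patients who stop treatment before 12 weeks still have outcomes collected at 12 weeks, because the analysis is by intention to treat.

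**The concern.** The effect on GP workload and the cost-effectiveness of community care are outcomes meant to inform commissioning. Any extra load that community delivery places on general practice could well fall on patients who run into difficulty, and some of these will die, withdraw or be moved to hospital. If their GP contacts are not requested, or are counted over fewer weeks, the community arms can look cheaper for primary care than they are.

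The CSRI has a related weakness. EQ-5D is taken at baseline, 4, 8 and 12 weeks, but resource use after baseline is asked about once. A patient who withdraws at week 10 can contribute three EQ-5D scores and no follow-up CSRI, so QALYs and costs would rest on different sets of patients.

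Because only community patients can be withdrawn through transfer, the loss need not be balanced across arms.

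**Working it through.** **Step 1: what completion means.** The GP section does not define it. There are two readings.

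- *Completion means reaching 12 weeks.* Patients who die or withdraw earlier trigger no letter.
- *Completion includes early withdrawal*, as under Study interventions. The letter goes out, but the trial period over which contacts are counted may end at withdrawal, so counts cover unequal windows.

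Neither reading settles what happens after a death, and neither supplies a follow-up CSRI before week 12.

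**Step 2: who is affected.** Under Study duration, patients who only stop treatment stay in 12-week collection, so they are not part of the gap. Those who die or withdraw from the trial are. A transferred patient falls between two statements: withdrawn under Recording and collection of data, but covered by the intention-to-treat principle under Study duration.

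**Step 3: what other sources supply.**

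- Cancer drugs: "Use of the specific cancer drug treatments is centrally recorded". Complete for drugs, silent on the rest.
- Treatment nurses: "They are asked to document all scheduled and unscheduled contact with their patients as well as working hours relating to treatment of trial patients". Covers nurse time, not GP visits for other reasons.
- Prescribing: "records of drugs prescribed by the hospital and the patient's own GP will be obtained". This covers drugs, not contacts, and the only route described for GP prescriptions is the print-out requested in the same letter.
- Diaries: unscheduled contacts about the current course of treatment, GP included, up to the final trial visit. The GP review is wider and also covers other treatment needs, support and advice.
- SAE reports: hospitalisations and deaths.
- "Service use information is typically provided by the patient and/or family members (supplemented where possible with administrative data from providers". This back-up is conditional, and no collection at exit is scheduled.

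What remains exposed is the full GP-contact count and the CSRI items on travel, informal care and time off work.

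**Step 4: how large it could be.** The article gives no figure for this outcome, so there is none to reproduce. The following rests on assumptions. Set the completer mean to 1 in every arm. Let *d* be the share without data and *r* the care they use relative to completers.

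True arm mean = (1 − *d*) + *d·r*. A completers-only mean understates it by 1 − 1/[(1 − *d*) + *d·r*]:

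- *d* = 10%, *r* = 2: 1 − 1/1.1 = 9.1%
- *d* = 20%, *r* = 2: 1 − 1/1.2 = 16.7%
- *d* = 30%, *r* = 2: 1 − 1/1.3 = 23.1%
- *r* = 1: 0% for any *d*

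Hidden community-minus-hospital difference = (*d*_C − *d*_H)(*r* − 1). With *d*_C = 30% and *d*_H = 10%:

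- *r* = 1.5: 0.20 × 0.5 = 0.10
- *r* = 2: 0.20 × 1 = 0.20
- *r* = 3: 0.20 × 2 = 0.40

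With 20% against 10% these halve to 0.05, 0.10 and 0.20. With equal shares and the same *r* in each arm, the difference is 0. For total cost these are upper bounds at the assumed rates, because several cost components do not depend on reaching week 12.

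On the second reading, suppose withdrawn patients have the completers' weekly rate but are counted for half the window. The observed means are 0.70 + 0.30 × 0.5 = 0.85 (community) and 0.90 + 0.10 × 0.5 = 0.95 (hospital). That is an apparent difference of −0.10 where the true one is 0.

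**The case against.** The strongest reply is that the GP section states when a retrospective request is made, not who is excluded. It does not say that only completers are covered, and the article elsewhere counts early withdrawal as a form of completion. A reader might infer that GP data are restricted to those who reach week 12; the text does not establish that. This stands. It does not remove the problem, because the broader reading leaves the window open and deaths unaddressed.

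A reader might also infer that resource use as a whole is missing for early leavers. It is not: drug records, nurse logs, diaries, SAE reports and prescribing records cover part of it, and patients who only stop treatment remain in 12-week collection.

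Nor does the article show that leavers use the most care. That is plausible but has no figure behind it. If *r* were below 1, as it could be where death cuts the period short, the bias would reverse. Patients with life expectancy under 6 months are excluded and the local policy selects low-risk patients and treatments, so early deaths may be few.

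It is tempting to apply the 30% allowance from the Sample size section and say that 0.30 × 130 = 39 patients per arm would have neither record. That allowance concerns the primary outcome and includes unreturned questionnaires. A patient who skips the QLQ-C30 still has GP notes, so 39 is at most a ceiling.

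Finally, an article condenses a fuller protocol, and exit procedures may be described there. For that reason the point rests on the trigger, schedule and withdrawal rule that the article does state, not on what it leaves out.

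**Conclusion.** The point holds in a limited form. Followed as written, the stated rules can leave patients who die or withdraw from the trial with no GP-contact count or a truncated one, and with no follow-up CSRI. The transfer rule means this can happen more often in the community arms. The GP-resource and cost comparisons are at risk; collection of the primary quality-of-life score is a separate matter.

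The size is unknown. The hidden difference of 10% to 40% of the completer mean depends on assumed exit shares of 10% and 30% and use ratios of 1.5 to 3. It vanishes if leavers use care as completers do, or if exit shares and use ratios are equal across arms. The change is worth making because it is cheap and the data may not be recoverable later.

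**What to change.** 1. **Impact of treatment on local GP resources:** send the GP request 12 weeks after the start of the study period for every randomised patient, including those transferred, withdrawn or dead, unless consent to record access was withdrawn. Ask for contacts over a fixed 12-week window, or to death if earlier.
2. **Service use and cost data, and Table 1:** also give the CSRI at the early-withdrawal review already held under Study interventions, covering the time since baseline.
3. **Study duration and Recording and collection of data:** reconcile the two statements so that transferred patients stay in 12-week data collection. This concerns data only, not when a patient should be transferred.

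The cost is an amendment, some extra letters with the small GP payment already provided for, and one more use of an existing form at an existing visit. The downside is that part-period CSRI costs must be combined with full-period ones in the analysis. Patients who die before an exit review will still lack a follow-up CSRI; for them the GP notes are the recoverable part.
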